### Data Analysis

SPSS software (version 29; IBM) and SAS (version 9.4; SAS Institute) will be used for data analysis. Descriptive statistics will be computed to characterize the study samples and outcomes. The NOL signal quality will be checked for all enrolled patients to ensure the accuracy of the data. As done in previous studies, NOL values will be averaged within 15 seconds before and after the peak value obtained after the start of each nonnociceptive procedure (7 NOL values total around the peak for soft touch and NIBP) and nociceptive procedure. In addition, NOL values will be averaged over a 1-minute period at rest before and after the procedure. CPOT scores will be obtained independently by 2 trained raters, one at the bedside and one who will view the patient videos at a later time. Intraclass correlation coefficients (ICC) will be calculated between the CPOT scores of both raters during procedures. ICC>0.80 will confirm excellent interrater reliability [28].

For objective 1 (criterion validation), the receiver operating characteristic (ROC) curve [43] will be performed to examine the ability of the NOL to adequately classify patients with pain. In patients able to self-report (Group A), an established pain intensity score >4 based on participants’ self-reports as the reference standard criterion indicating moderate to severe pain will be used [10,44]. This criterion is also commonly used in practice to support clinical decisions in the administration of opioids. A ROC curve will be obtained for each nociceptive procedure (a total of 2 procedures per patient). In patients unable to self-report but in whom behaviors can be observed (Group B), we will use the determined CPOT score >2 as the alternative reference criterion, which is associated with the presence of moderate to severe pain [44]. Again, for Group B, a ROC curve will be obtained for each nociceptive procedure (total of 2 procedures per patient) [45]. As a supplementary analysis, we will perform ROC curves for repeated-measures design in each group (A and B) and compare them [46]. In addition, considering that the CPOT will be available in Group A and Group B, ROC curves will be performed in each group separately to compare the AUC of independent curves for each of the 2 procedures [45]. The NOL cutoff value that will optimize both sensitivity and specificity will be determined.

Discriminative validation (objective 2) is our main objective to test in Group C, and paired *t* tests comparing the NOL values of each nociceptive procedure with the nonnociceptive procedure will be obtained. Generalized linear mixed model for repeated measures will allow us to compare the NOL index values across time points (pre, during, and post), procedures (nonnociceptive vs nociceptive), and their interaction in each group (A, B, and C). The generalized linear mixed model technique incorporates the full-information maximum likelihood procedure, which allows parameter estimation for missing data [47]. NOL values are expected to be significantly higher during nociceptive procedures in all 3 groups. Covariates (eg, sex, gender, morphine equivalent doses, opioid use before ICU admission) may be added if appropriate. Finally, NOL data obtained at pre- and postadministration of an opioid dose will be tested separately using paired *t* tests as not all patients will be candidates for these assessments.

For test-retest reliability (objective 3), paired *t* tests will be performed between pre and post-nonnociceptive and nociceptive procedures in all 3 groups. Nonsignificant paired *t* tests are expected to support the stability of NOL values when the patients are at rest.

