### Potential Limitations and Mitigation Strategies

Recruiting ICU patients or obtaining written consent from the persons qualified to consent for them is challenging. This requires daily screening of eligible patients and close follow-up. Support from the nursing staff and physicians is key to identifying eligible patients and approaching those qualified to consent for them. Our research team has developed efficacious recruitment procedures, trained competent research staff, and established close collaboration with ICU care teams in all sites, which facilitate the implementation of this study. The feasibility of recruitment was also demonstrated in our pilot work. A screening log will be completed at each site to compile eligibility criteria and reasons for refusals, losses, or withdrawals. In our pilot studies [26,27], we were unsuccessful in obtaining data from some participants mainly due to missing the procedure, either because temporary fellows forgot to inform the research team or the procedure occurred after ICU discharge. Chest tube removal and endotracheal suctioning were the sole nociceptive procedures included in our pilot studies. Broadening the selection of nociceptive procedures may reduce the number of missed observations of these events. However, we may still miss some procedures due to urgent situations. Also, data collection will be planned as soon as possible after obtaining written consent to minimize losses. In addition, we will document any challenges related to the use of NOL (eg, absence or loss of signal) and troubleshooting strategies. Finally, CPOT raters cannot be blinded to the procedures they will view on the videos. As a result, they may anticipate patients’ behavioral responses to the procedure, which may influence their ratings. The examination of interrater reliability of CPOT scores involving trained research staff from different settings and using 2 methods of rating (bedside and video) may help minimize this potential bias.

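### Agreement between two CPOT raters who both know the procedure measures reproducibility; it cannot reduce an expectation they share, and the planned ICC does not test the CPOT >2 class that the Group B ROC uses

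*Protocol article*

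**What the plan says.** Methods, Data Analysis, fixes the raters: "CPOT scores will be obtained independently by 2 trained raters, one at the bedside and one who will view the patient videos". It fixes the data and the rule: "Intraclass correlation coefficients (ICC) will be calculated between the CPOT scores of both raters during procedures. ICC>0.80 will confirm excellent interrater reliability". In this protocol the word procedures covers both kinds. The procedure list names soft touch and cuff inflation as nonnociceptive, and Table 1 schedules behavioral scores at both in Groups A and B.

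The same section makes the CPOT the pain label for the Group B ROC curves, one per nociceptive procedure: "we will use the determined CPOT score >2 as the alternative reference criterion". The sample size section confirms that Group B has no self-report.

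Potential Limitations and Mitigation Strategies concedes that "CPOT raters cannot be blinded to the procedures they will view on the videos" and that "they may anticipate patients’ behavioral responses to the procedure, which may influence their ratings". It then says that examining interrater reliability with trained staff from different settings and "using 2 methods of rating (bedside and video) may help minimize this potential bias".

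**The concern.** Two separate matters arise.

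First, the mitigation does not match the bias. The admitted problem is that a rater who sees suctioning or a drain removal may score what is expected. The second rater sees the same event on video. Where both lean the same way, agreement is preserved, so a high ICC says nothing about whether the lean is there.

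Second, the reliability measure is not aimed at the quantity that matters most. The Group B ROC needs raters to agree on who is above 2 during nociceptive procedures. An ICC of total scores does not report that, and the stated wording leaves room to include painless readings, whose low scores would widen the spread and raise the coefficient.

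At stake is how the Group B result is read. If the label is noisy or partly driven by expectation, a low AUC may be put down to the NOL, and readers may take the reported ICC as reassurance on a point it does not address.

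**Working it through.** The 0.80 threshold is a convention with no derivation to reproduce. The CPOT range (0 to 8), the cut at >2, the two raters and 50 patients in Group B come from the protocol. All CPOT means and SDs below are assumptions, because the protocol gives none.

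**1. A shift common to both raters**

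Let a score be patient signal (SD s) + shift d shared by both raters + independent rater error (SD e). Then ICC = s²/(s² + e²), and d does not appear. Scores are whole numbers, so CPOT >2 means a latent value of at least 2.5. With a latent mean of 2.5, the share above 2 is Φ(d/√(s² + e²)).

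With s = 1.8 and e = 0.6, √(3.24 + 0.36) = 1.897. With s = 1.6 and e = 0.5, √(2.56 + 0.25) = 1.676. The ICCs are simulated after rounding and limiting scores to 0–8.

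| Shared shift d | Share >2 (s 1.8, e 0.6) | ICC | Share >2 (s 1.6, e 0.5) | ICC |
|---|---|---|---|---|
| 0 | 50% | 0.87 | 50% | 0.88 |
| 0.5 | 60% | 0.88 | 62% | 0.88 |
| 1.0 | 70% | 0.88 | 73% | 0.88 |
| 1.5 | 79% | 0.88 | 81% | 0.88 |

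The label changes for about 30% of patients and the ICC does not move.

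**2. An expectation that varies between procedures**

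If the shared expectation differs across readings with variance v, ICC = (s² + v)/(s² + v + e²), so it raises the ICC. As an illustration, assume expected scores of 1 to 5 across nociceptive types, behavior SD 1.5 and rater error SD 0.5. As the weight of the patient's own behavior in the score falls through 1, 0.5, 0.25 and 0, the AUC of an assumed NOL falls through 0.77, 0.66, 0.59 and 0.50. The ICC is 0.92, 0.87, 0.85 and 0.84, above 0.80 throughout.

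**3. Pooled versus nociceptive-only agreement**

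Suppose half the readings are painless and half nociceptive, and scores carry only the procedure type. With expected scores m0 and m1, the between-reading variance is ((m1 − m0)/2)².

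- 0 versus 3, error SD 0.7: 2.25/(2.25 + 0.49) = 0.82.
- 0 versus 3, error SD 0.9: 2.25/(2.25 + 0.81) = 0.74.
- 1 versus 3, error SD 0.7: 1/(1 + 0.49) = 0.67.

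Within a single procedure type the ICC is then about 0.

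Now add a patient signal of SD 0.75 to the nociceptive readings, with mean 2.5 to 3 and rater error SD 0.75; painless rater error SD is 0.4, with 50 patients and two readings of each kind. The ICC within nociceptive readings is 0.46 and kappa at >2 is about 0.32, whatever the painless mean. The pooled ICC does depend on it:

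| Painless mean | Pooled ICC | Simulated studies with pooled ICC >0.80 |
|---|---|---|
| 0 | 0.82–0.86 | about 83–100% |
| 0.5 | 0.74–0.80 | about 1–55% |
| 1 | 0.66–0.75 | about 0–3% |

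With a patient signal of SD 2 instead, the ICC within nociceptive readings is about 0.85 and kappa about 0.68, so the gap nearly closes. Pooling can mislead, but whether it would here is unknown.

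**The case against.** The Data Analysis sentence claims interrater reliability, and an ICC is a proper measure of that. It remains a useful check on random rater error. A reader might infer that the rule certifies the CPOT as a valid reference standard, but the protocol does not say so. It supports CPOT validity separately, under the description of the tool, from published studies against self-report. Nor does the ICC gate any analysis. This stands.

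The text does not say that painless and nociceptive readings will go into one coefficient; it speaks of coefficients in the plural, and the ROC curves are run per nociceptive procedure. A reader might also take high pass rates for procedure-only scoring as what to expect. They need a painless mean near 0 and fall away at 0.5 to 1, and the protocol's own background says many ICU patients have pain at rest. This stands too, so the pooling point is conditional.

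A reader might call it an error that 0.80 is applied to a point estimate without a lower confidence bound. That is a reporting preference.

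The limitation is disclosed, and the mitigation is hedged. Raters from different settings could expose expectations that differ between them. But the hedge does not supply the missing mechanism: the part of the expectation that both raters hold leaves no trace in their agreement. The safeguards around self-report timing act in Group A and do not concern knowledge of the procedure.

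**Conclusion.** The point holds in two parts. The first needs no assumption about pooling: agreement between two raters who both know the procedure cannot detect or reduce an expectation they share, so it should not be offered as mitigation. The size is illustrative: under assumed signal SDs of 1.6 to 1.8 and error SDs of 0.5 to 0.6, a common shift of up to 1.5 points moves the share with CPOT >2 from 50% to about 80% with the ICC at about 0.88.

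The second part is that the planned ICC does not report agreement on the CPOT >2 class during nociceptive procedures, the class on which the Group B ROC rests. If painless readings were pooled in, the ICC could exceed 0.80 with nociceptive-only agreement near 0.46; the frequency cannot be stated from the protocol. This is a worthwhile improvement to the plan and does not undermine the use of an ICC as such.

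**What to change.** In Data Analysis, compute the ICC within nociceptive procedures, separately for Groups A and B, and report painless procedures separately. Add kappa, or positive and negative agreement, for CPOT >2. Give 95% intervals that account for two procedures per patient, for example by resampling patients.

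In Potential Limitations and Mitigation Strategies, limit the interrater claim to reproducibility and state that expectation bias shared by both raters remains.

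The cost is a few sentences of text and some extra output from scores already being collected; no new patients, raters or measurements are needed. The downside is that the reported agreement may be lower and its interval wider.

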### Study Rationale, Goal, Objectives, and Research Hypotheses

An instrument can only be shown as valid for a specific purpose in a given population and context [28]. The NOL index was initially developed and validated for nociception monitoring and related pain in anesthetized patients [17,19-25]. Therefore, validating its use for nociception (primary purpose) and pain assessment (related purpose) in critically ill adults admitted to the ICU (different population and context of care) is necessary. Inspired by our pilot work, strategies for this larger validation study include: (1) criterion validation (ie, NOL’s ability to detect pain according to pain standard criteria) and (2) discriminative validation (ie, NOL’s ability to discriminate between nonnociceptive and nociceptive procedures) [28]. Considering that reliability is a necessary condition for validity [28], test-retest reliability of the NOL’s ability to generate consistent values in similar conditions (eg, at rest) will also be examined.

Research Question: Is the NOL a valid method for the assessment of nociception and pain in critically ill adults in the ICU context?

In order to answer this research question, specific validation objectives are to examine the NOL’s ability to:

Detect pain in ICU patients able or not to self-report using appropriate pain standard criteria (ie, criterion validation);Discriminate between nonnociceptive and nociceptive procedures part of standard care as well as before and after the administration of a breakthrough opioid dose (ie, discriminative validation);Generate consistent values in similar conditions (ie, pre- and post-nonnociceptive and nociceptive procedures) when ICU patients are at rest.

Our research hypotheses to be tested include:

H1. The NOL index adequately classifies ICU patients with pain based on either their self-reported pain intensity or CPOT scores.

H2. The NOL index produces higher values during nociceptive procedures compared to nonnociceptive procedures and lower values post- versus preopioid administration.

H3. The NOL index generates consistent values pre- and post-nonnociceptive and nociceptive procedures when ICU patients are at rest.

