### Variables and Measurement Tools

#### Primary Measure: The Nociception Level (NOL) Index–All Groups (A, B, and C)

The Pain Monitoring Device-200 (PMD-200; Medasense Biometrics Ltd; Figure 1) is used in this study. PMD-200 offers the multiparametric NOL index (0-100) and was approved by Health Canada for clinical use in September 2017. The NOL captures several physiological parameters simultaneously through a finger probe and disposable sensor, which includes 4 small sensors, sampled 50-500 Hz: (1) accelerometer, (2) photoplethysmograph, (3) galvanic skin response, and (4) peripheral temperature. From these 4 sensors, the following physiological parameters are extracted: heart rate, heart rate variability, photoplethysmography pulse wave amplitude, skin conductance level, number of skin conductance fluctuations, skin temperature, and their time derivatives. All these parameters are integrated and analyzed simultaneously using a Random Forest machine learning model approach to provide the NOL index, which can range from 0 to 100 [17]. A NOL cutoff value >25 for the detection of self-reported pain was found in our pilot study with ICU cardiac surgery patients [27].

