### Sample Size Calculation

The primary objective is to validate the NOL using pain standard criteria (ie, self-report and CPOT scores). Therefore, ROC is considered our primary analysis and guides the sample size calculation for Group A and Group B. Power calculations were based on our pilot findings [26,27] and results from previous ICU studies considering a clinically acceptable AUC of 0.75 [42] (using a null hypothesis of AUC=0.50) with a power of 80% and an adjusted α of .025 (2 ROC curves for each procedure in each group). For Group A in whom the self-report of pain is obtained and using a ratio of 2:1 in pain:no pain cases according to self-reported pain intensity scores of <4 and >4, a sample of 54 patients is required. For Group B in whom only the CPOT scores are available and using a ratio of 1.5:1 in pain:no pain cases according to CPOT scores of <2 (no pain) and >2 (pain), a sample of 50 patients is necessary. For Group C (unable to self-report and express behaviors), we will not be able to use any pain standard criterion. Therefore, our main objective is to test whether the NOL can discriminate between a nociceptive procedure and a nonnociceptive procedure. In order to detect a minimal mean increase of 10 in the NOL value during the nociceptive procedure (with a standard deviation of 10 as found in our pilot findings), a minimal sample size of 13 patients is required to run paired *t* tests with a power of 80% and an α of .01 (to account for multiple test comparisons). Considering an attrition rate of 25% (data collection was completed in 73% of consenting patients in our pilot work), recruitment targets include 68 patients in Group A, 62 patients in Group B, and 16 in Group C for a total of 146 ICU patients. Power calculations were performed by a statistician using Power and Precision 4 (Biostat Inc).

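### The NOL cutoff is to be chosen on the study data while the pilot cutoff >25 goes unevaluated; accuracy read at the new cutoff would be optimistic, and rejecting AUC = 0.50 shows only better-than-chance discrimination

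*Protocol article*

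**What the plan says.** H1 (Study Rationale, Goal, Objectives, and Research Hypotheses) reads: "The NOL index adequately classifies ICU patients with pain based on either their self-reported pain intensity or CPOT scores". It carries no numerical criterion.

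The Sample Size Calculation section makes ROC the primary analysis and sizes Groups A and B "considering a clinically acceptable AUC of 0.75 [42] (using a null hypothesis of AUC=0.50"), "with a power of 80% and an adjusted α of .025". This gives 54 patients in Group A, "using a ratio of 2:1 in pain:no pain cases", and 50 in Group B at 1.5:1.

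The section on the primary measure states: "A NOL cutoff value >25 for the detection of self-reported pain was found in our pilot study with ICU cardiac surgery patients". The Introduction (Background) reports the same value as adequate for classifying moderate to severe self-reported pain.

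Data Analysis plans one ROC curve per nociceptive procedure in Groups A and B, a repeated-measures ROC supplement and comparisons of AUC between groups. It ends the paragraph with: "The NOL cutoff value that will optimize both sensitivity and specificity will be determined". The value >25 does not appear there, and no AUC is named as the level at which classification counts as adequate.

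**The concern.** There are two related difficulties.

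**Cutoff.** A threshold chosen to look best in a small sample looks better there than it will in the next patients. The study's declared purpose is validation and a threshold from earlier data is already available. As written, the study would add another sample-specific threshold and leave the existing one unchecked. The article's Conclusion foresees the NOL guiding pain management in patients who have no other measure. Bedside use of that kind depends on a threshold and on honest error rates at it.

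**Reading of the AUC test.** H1 speaks of adequate classification, but the only reference value given for inference is 0.50. Data Analysis does state what result will count for the other properties: an ICC above 0.80 for rater agreement and nonsignificant paired tests for stability at rest. It gives no counterpart for objective 1. A significant result against 0.50 could therefore be reported as adequacy.

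**Working it through.** **Inputs from the Sample Size Calculation section.** Alternative AUC 0.75, null AUC 0.50, α 0.025, power 80%. Group A has n = 54 at 2:1, i.e. 36 pain and 18 no pain. Group B has n = 50 at 1.5:1, i.e. 30 and 20. Sidedness is not stated.

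**1. Reproducing the plan's sample sizes.** One-sample z test of the AUC, with null variance (n1 + n0 + 1)/(12·n1·n0) and Hanley-McNeil variance at the alternative:

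- Two-sided α 0.025 gives minimum totals of 52 (A) and 49 (B). Rounding up to whole 2:1 and 1.5:1 splits gives exactly 54 and 50.
- One-sided 0.025 gives 43 and 40, which does not match.

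The stated sizes are therefore right for a two-sided test against 0.50.

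**2. Smallest observed AUC that rejects 0.50** (z = 2.241):

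- A: 0.5 + 2.241·√(55/(12·36·18)) = 0.5 + 2.241·√(55/7776) = 0.689
- B: 0.5 + 2.241·√(51/(12·30·20)) = 0.5 + 2.241·√(51/7200) = 0.689

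**3. Standard error at an AUC of 0.75 (Hanley-McNeil).** With A/(2−A) = 0.6, 2A²/(1+A) = 0.6429 and A² = 0.5625:

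- A: √[(0.1875 + 35·0.0375 + 17·0.0804)/648] = 0.0665. The 95% CI for an observed 0.75 is about 0.62 to 0.88. Power is Φ((0.75 − 0.6885)/0.0665) = 82%.
- B: √[(0.1875 + 29·0.0375 + 19·0.0804)/600] = 0.0683. The 95% CI is about 0.62 to 0.88 and power is 82%.

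The same formulas give the probability of significance per curve at lower true values: 31% at an AUC of 0.65 and 56% at 0.70, in both groups.

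**4. Optimism of a re-optimised cutoff.** NOL values are drawn as N(d, 1) with pain and N(0, 1) without, where d = √2·Φ⁻¹(AUC). In each of 20,000 data sets per setting, the cutoff c that maximises J = sensitivity + specificity − 1 is chosen. Apparent J is read from the same data. True J at that cutoff is Φ(c) − Φ(c − d).

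| True AUC | Split | Apparent J | True J at chosen cutoff | Overstatement |
|---|---|---|---|---|
| 0.75 | 36:18 | 0.467 | 0.335 | 0.132 |
| 0.75 | 30:20 | 0.469 | 0.337 | 0.132 |
| 0.65 | 36:18 | 0.336 | 0.187 | 0.149 |
| 0.65 | 30:20 | 0.336 | 0.187 | 0.148 |
| 0.50 | 36:18 | 0.163 | 0 | 0.163 |
| 0.50 | 30:20 | 0.164 | 0 | 0.164 |

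At a true AUC of 0.75 the best J any cutoff could reach is 2Φ(d/2) − 1 = 0.367. For 36:18, apparent sensitivity and specificity average about 0.74 and 0.73, against about 0.69 and 0.64 truly achieved. The chosen cutoff varies from sample to sample with an SD of about 0.45 within-class SDs. The within-class SD of the NOL is not given; if it lies between 10 and 20 points (assumed), that is 4.5 to 9 NOL points.

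**5. Precision available at a fixed cutoff.** Exact 95% CIs for illustrative counts (assumed):

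- Group A: sensitivity 27/36, 58% to 88%; specificity 14/18, 52% to 94%.
- Group B: sensitivity 22/30, 54% to 88%; specificity 15/20, 51% to 91%.

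**The case against.** Much can be said for the plan as it stands.

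- **The AUC uses no cutoff.** The primary analysis is the ROC curve, so cutoff optimism cannot bias it. This stands. A reader might infer that the study's only accuracy analysis is circular and that nothing is validated. The document does not support that: several AUC analyses are planned, and the problem is confined to accuracy at the cutoff.
- **Neither 0.75 nor >25 is declared a benchmark for H1.** This also stands. The first is the power alternative and the second a pilot finding; the article promises to test neither. Powering 0.75 against 0.50 is standard and the arithmetic is correct. Nor does the article call AUCs below 0.75 too low, so one cannot say that it would accept a value it rejects elsewhere. Rejecting 0.50 when the true AUC is 0.65 or 0.70 is a correct rejection. It misleads only if reported as adequacy.
- **Looking again for a cutoff is reasonable.** The pilot value came from self-reporting cardiac surgery patients, and the two pilot studies covered only two nociceptive procedures. This study has broader patients, more procedures and, in Group B, a CPOT criterion. That justifies an exploratory search and makes >25 only an indirect reference in Group B. It does not justify leaving >25 unreported in Group A, where the criterion is the same.
- **Detail may sit in an analysis plan not shown.** Bootstrap correction and interval methods could well be there, and their absence from an article is no fault. What remains is what the article does state: a cutoff will be derived from these data, with the known one not taken up.

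**Conclusion.** The point holds in a limited form. If sensitivity and specificity at the new cutoff are read from the data that chose it, their sum is overstated by about 13 percentage points at a true AUC of 0.75, and somewhat more at lower true AUCs. The pilot cutoff would meanwhile remain unevaluated. The AUC estimates are unaffected. A significant test against 0.50, possible from an observed AUC of about 0.69, supports better-than-chance discrimination and does not by itself establish adequacy.

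The size rests on these assumptions: equal-variance normal NOL values, a Youden-type optimum, the planned pain ratios, one observation per patient per curve, and a two-sided α of 0.025.

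A reader might go on to ask for a formal test against 0.75 or a rule that the AUC estimate must reach 0.75. Neither is supportable here. With 0.75 as the null, Group A would need about 196 patients even if the true AUC were 0.85. A pass rule at 0.75 would succeed only about half the time (about 52% in simulation) when the true AUC is exactly 0.75, against about 81% for the planned test.

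**What to change.** 1. **Group A:** report sensitivity and specificity with exact 95% CIs at the fixed pilot cutoff NOL >25, for each procedure, as the confirmatory cutoff result.
2. **Group B:** report the same as a secondary check, noting that >25 was derived against self-report and not the CPOT.
3. **New cutoff:** label it exploratory and give bootstrap optimism-corrected sensitivity and specificity beside the apparent values. The bootstrap must repeat the cutoff search in each resample.
4. **AUC:** report each with its CI. State that rejecting 0.50 supports only better-than-chance discrimination, and that adequacy will be judged by the estimate and interval against the 0.75 that the Sample Size Calculation section calls clinically acceptable. Set no hard pass threshold.

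No extra patients or data are needed. Recruitment is planned until 2026, so the wording can be fixed before the ROC analyses are run. The cost is a little more analysis, wide intervals at the fixed cutoff (Group A specificity rests on about 18 patients), and accuracy figures that will look less favourable than the apparent ones.

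### Resting consistency of the NOL (H3) is judged by nonsignificant paired t tests, which examine the mean shift and not agreement

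*Protocol article*

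**What the plan says.** The hypothesis is set out in the Study Rationale section: "The NOL index generates consistent values pre- and post-nonnociceptive and nociceptive procedures when ICU patients are at rest". The same section explains why it is tested: "Considering that reliability is a necessary condition for validity".

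The Data Analysis section gives the method for objective 3: "paired *t* tests will be performed between pre and post-nonnociceptive and nociceptive procedures in all 3 groups". It then says how the result will be read: "Nonsignificant paired *t* tests are expected to support the stability of NOL values when the patients are at rest".

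Nothing else in the article bears on NOL test-retest reliability. No ICC, limits of agreement, confidence-interval rule, equivalence margin or alpha is given for it. An agreement coefficient appears only for a different measure, the behavioral score: "Intraclass correlation coefficients (ICC) will be calculated between the CPOT scores of both raters during procedures". The Sample Size Calculation section sizes Groups A and B for the ROC analyses ("a sample of 54 patients is required" and "a sample of 50 patients is necessary") and Group C for the contrast between procedures ("a minimal sample size of 13 patients is required to run paired *t* tests with a power of 80% and an α of .01"). Objective 3 drives none of these numbers.

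**The concern.** Consistency on retest means that a patient's second resting value is close to the first, relative to the differences between patients. A paired t test asks only whether the average change is zero. Readings can scatter widely and independently around an unchanged mean, and the test will still usually be nonsignificant. Nonsignificance is also not evidence of equality, because it can come from few patients or a noisy signal. The rule errs in the other direction too: a device with excellent agreement and a small systematic shift will fail once the group is large enough to detect the shift.

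Because the article makes reliability a precondition for validity, a reassuring answer to objective 3 will be carried into the overall conclusion about the device. As planned, that answer would not carry the meaning given to it. Protection against drift is weakest in Group C, where no pain standard is available as a check.

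**Working it through.** **Inputs.** Evaluable patients are 54 (A), 50 (B) and 13 (C), from the Sample Size Calculation section. The SD of 10 is also from there. It concerns the increase during a nociceptive procedure, so its use for resting pre-post differences is an assumption, and a range of 8 to 20 is shown. Two-sided alpha .05 is likewise assumed, with .01 (the Group C paired-t level) as an alternative.

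**The plan's own figure.** Objective 3 has none. The only paired-t calculation is Group C's 13 patients for a difference of 10, SD 10, alpha .01 and 80% power. With effect size 10/10 = 1, an exact one-sided t test at n = 13 has 80.6% power, so 13 is reproduced when 10 is read as the SD of the paired difference. The article does not state the sidedness.

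**1. No mean shift.** The t statistic is mean(d) / (SD(d)/√n). Correlation between pre and post values changes SD(d) = σ√(2(1−ρ)), but the statistic is scaled by that same SD, so P(nonsignificant) = 1 − alpha for any ρ. Simulation with 100,000 samples per setting gave:

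| Correlation | n = 13 | n = 54 |
|---|---|---|
| 0 | 95.0% | 95.0% |
| 0.3 | 95.1% | 95.0% |
| 0.9 | 95.0% | 95.0% |

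Pure noise passes each test as often as a highly reliable device.

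**2. All tests together.** Each group has one nonnociceptive pre/post pair and one or two nociceptive pairs: 3 × 2 = 6 to 3 × 3 = 9 tests. If these were independent, all would be nonsignificant with probability 0.95^6 = 0.74 to 0.95^9 = 0.63, again whatever the ICC. The article gives no rule for combining them.

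**3. A true resting drift of 5 points.** P(nonsignificant) from the noncentral t distribution, noncentrality 5√n/SD (for SD 10: 1.80 at n = 13 and 3.67 at n = 54):

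| SD of differences | alpha | n = 13 | n = 50 | n = 54 |
|---|---|---|---|---|
| 8 | .05 | 46% | 0.9% | 0.5% |
| 10 | .05 | 62% | 6.6% | 5.0% |
| 14.14 | .05 | 78% | 31% | 28% |
| 20 | .05 | 87% | 59% | 56% |
| 10 | .01 | 84% | 20% | 16% |

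The SD of 14.14 = 10√2 applies if 10 were the SD of single readings and pre and post were uncorrelated.

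**4. Largest observed mean shift that stays nonsignificant**, t(0.975, n−1) × 10/√n: 6.04 points at n = 13, 2.84 at n = 50 and 2.73 at n = 54.

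**5. The converse error.** Take σ = 10, ρ = 0.95 and a 2-point shift. Then SD(d) = 10√(2 × 0.05) = 3.16, and the absolute-agreement ICC is about 0.95 × 100/(100 + 2²/2) = 0.93. The test is significant in over 99% of samples at n = 50 or 54, so good agreement would be read as instability.

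**6. What the alternatives would deliver.** Fisher-z interval for an observed ICC of 0.80: about 0.48 to 0.93 at n = 13 (0.45 to 0.94 with the more conservative n − 3 divisor), 0.67 to 0.88 at n = 50 and 0.68 to 0.88 at n = 54. Two one-sided tests with an illustrative ±5 margin (SD 10, zero drift, one-sided 5%) have about 13% to 14% power at n = 13, 93% at n = 50 and 95% at n = 54.

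**The case against.** Three defences deserve a hearing. First, an article condenses a fuller plan. That does not help here, because the method and its reading are stated rather than left out. Second, the mixed model also uses the pre and post values. As described, however, it compares mean NOL values across time points and procedures, so it leaves the same gap. Third, the article says nonsignificance is expected to support stability, which is softer than a formal decision rule. That is true, but no other basis for H3 is offered.

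Some stronger readings are tempting and do not hold:

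- A reader might infer that 95% of studies would support H3 for a useless device. The 95% is per test. Across all the tests the figure is 63% to 74% under independence.
- A reader might infer that small groups always pass more easily. With exactly zero shift the pass rate does not depend on sample size. The advantage of small or noisy groups appears only when there is a real mean shift.
- A reader might infer that H3 would be supported almost regardless of true reliability. This is fair for random noise but not for systematic drift: at SD 10 and alpha .05, Groups A and B would detect a 5-point drift more than 93% of the time.
- A reader might infer that the plan adopts alpha .05 here. It states no level for objective 3.

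It also stands that the ROC analysis is primary, and that objectives 1 and 2 do not depend on this rule.

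**Conclusion.** The concern holds in this form: the only analysis planned for H3 cannot answer it. Two results need no assumption about the SD. The test is insensitive to agreement when there is no mean shift, and nonsignificance is not evidence of equality. The size of the drift problem does rest on assumptions. At alpha .05 and SD 10, a 5-point resting drift is missed 62% of the time at 13 patients and 5.0% at 54. Over SD 8 to 20 the ranges are 46% to 87% and 0.5% to 56%.

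This should be fixed because the article makes reliability a precondition for validity. It does not threaten the primary analysis, and the documents do not support reading it as a flaw in the criterion or discriminative validation.

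**What to change.** Delete the sentence that takes nonsignificance as support for stability. For each group and each pre/post resting pair, report the absolute-agreement ICC with its 95% CI and the Bland-Altman bias with 95% limits of agreement, and make these the basis for H3. Show the mean pre-post difference with its CI. If a claim of no mean shift is wanted, test equivalence against a margin that the investigators prespecify and justify. The ±5 used above is only an illustration.

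The resting values are already being collected, so the change is to the analysis text and needs no new measurements. The cost is visible imprecision in Group C: an observed ICC of 0.80 at 13 patients has a 95% CI from roughly 0.45–0.48 to 0.93–0.94, and a ±5 equivalence test there would almost always be inconclusive. Group C should therefore be reported as estimates with CIs, without a pass/fail statement.
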